### Outcome measures

#### Primary

The primary outcome measure is the worst pain score experienced during burn dressing change (11-point numerical rating scale - NRS). The NRS has been selected as the patient does not have to be able to write, as is required for a graphical rating scale.

#### Secondary

The secondary outcome measures are as follows:Average pain scores during dressing change (NRS).Pain score 1 h after dressing change (NRS).Anxiety score during dressing change (NRS).Patient satisfaction with pain control, measured by Likert item in response to the following question:How satisfied were you with your overall pain management during your dressing change?Patient usability, measured by Likert items in response to the following questions:To what extent did you feel the VR equipment was easy to use?Have you enjoyed the VR session?To what extent did you feel you ‘went into’ the virtual world?How satisfied were you with the virtual reality system during your dressing change?Nausea experienced during the dressing change (Likert item).Nursing satisfaction with interactive distraction system, measured by Likert items in response to the questions:To what extent did you feel the VR equipment was easy to use?To what extent did you feel the VR equipment interfered with clinical care?

All but the nausea assessment has five possible responses: not at all, not really, undecided, somewhat and very much. The nausea Likert item consists of not at all, very briefly, some of the time, most of the time and all of the time. Each Likert item will be analysed individually.

Demographic data will include patient age, gender, size of burn, time since injury and pain score before the dressing change.

### Data analysis

Data will be analysed using IBM SPSS 20.0. Normality will be assessed using the Shapiro-Wilk Test. When comparing the three conditions the repeated measures analysis of variance (ANOVA), assuming normality, or the Friedman test will be used. When comparing passive or active VRET conditions to the control condition, the Wilcoxon signed rank test will be a possible alternative to a paired *t* test.

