### Sample size

Using a Monte Carlo method, we estimate that a sample size of 25 patients would provide 99 % power to detect a clinically important effect. The data and assumptions underlying the calculation are as follows:The observed distribution of 33 pain scores in a recent audit is the true distribution of the ‘control’ value.The mean percentage reduction from the control value is 30 for interactive VRET. This value has been chosen as it has been demonstrated that the patient-determined, clinically important improvement reduction in pain experienced corresponds to 33 % reduction in measured pain, using an 11-point numerical rating scale [32].The mean percentage reduction from the control value is 15 for passive VRET.Both percentage reductions are normally distributed with a standard deviation of 25.The nonparametric Friedman test (with a significance level of 5 %) will be used to compare the pain scores under the three conditions.

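### The Sample size section fixes the Friedman test, but the Data analysis section lets a normality result choose between ANOVA and Friedman, so the primary test is not settled before the data are seen

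*Protocol article*

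**What the plan says.** The Sample size section lists what the Monte Carlo calculation rests on. Its last item reads "The nonparametric Friedman test (with a significance level of 5" %), and it continues that this test "will be used to compare the pain scores under the three conditions". The headline result, a "sample size of 25 patients would provide 99" % power, is the power of that test.

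The Data analysis section reads differently. It says "Normality will be assessed using the Shapiro-Wilk Test", and then compares the three conditions by repeated measures ANOVA if normality is assumed, or by Friedman. For passive or active VRET against control, "the Wilcoxon signed rank test will be a possible alternative" to a paired t test. The section names no outcome, so it makes no exception for worst pain on the 11-point scale, which the Outcome measures section makes primary.

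The Hypothesis section concerns interactive VR against standard analgesia alone, so the pairwise active-versus-control test bears directly on it.

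**The concern.** One section states a fixed test, and the other makes that test conditional on the observed data. Read literally, they disagree on whether the primary analysis is settled. The pairwise comparison closest to the hypothesis has two candidate tests and no stated rule for choosing between them.

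At stake is who or what decides which p-value is primary. If a pre-test decides, the choice turns partly on chance in about 25 patients with whole-number scores. If the analyst decides, the nominal 5 % no longer describes the procedure.

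**Working it through.** **Inputs from the Sample size section.** 25 patients, three conditions each, and Friedman at 5 %. "The mean percentage reduction from the control value is 30 for interactive VRET"; "The mean percentage reduction from the control value is 15 for passive VRET"; "Both percentage reductions are normally distributed with a standard deviation of 25".

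**Inputs assumed, because the article does not give them.**
- The 33 audit scores are replaced by seven shapes on the 0 to 10 scale: normal with means 3, 5, 6 and 7, rounded and clipped; uniform 0–10; uniform 4–10; left-skewed.
- The correlation between the two reductions is 0 or 0.5.
- VRET scores are left unrounded or rounded to whole points.
- The normality rule is Shapiro-Wilk on the raw scores, with p > 0.05 required in all three conditions.

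**Step 1: the plan's own figure.** Control score C comes from the assumed shape. Interactive = C × (1 − R₁) with R₁ ~ N(0.30, 0.25²), and passive = C × (1 − R₂) with R₂ ~ N(0.15, 0.25²). The tie-corrected Friedman statistic is referred to chi-square on 2 df. There are 7 × 2 × 2 = 28 scenarios of 20,000 trials each. Power is 98.5 to 99.9 %, so the stated 99 % reproduces.

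**Step 2: which test would run.** All three conditions pass the assumed rule in 11 % of trials at the low end (mean 3, rounded, uncorrelated) and 64 % at the high end (mean 6, unrounded, correlation 0.5). Testing active-minus-control differences instead of raw scores changes the normality verdict in 13 to 60 % of trials, over two sets of simulations with four assumed control shapes and rounded scores. The selected test cannot be foreseen.

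**Step 3: power under the rule.** The two-stage rule gives 98.4 to 100 %, at worst 99 − 98.4 = 0.6 points below the stated figure. ANOVA throughout gives 97.4 to 100 %, or 95.8 to 100 % with the Greenhouse-Geisser correction.

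**Step 4: type I error.** Null model: a patient level from the assumed shape plus independent normal deviations (SD 1.7) per condition, rounded and clipped to 0–10, with 6,000 trials per shape. F and A are the rejection rates of Friedman and of Greenhouse-Geisser ANOVA, and D is the rate at which they disagree. The chance that at least one rejects is (F + A + D)/2.

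| Control shape | F | A | D | (F + A + D)/2 |
|---|---|---|---|---|
| mean 7 | 0.0485 | 0.0425 | 0.0420 | 0.0665 |
| mean 6 | 0.0498 | 0.0468 | 0.0377 | 0.0672 |
| left-skewed | 0.0412 | 0.0418 | 0.0363 | 0.0597 |
| mean 3 | 0.0508 | 0.0482 | 0.0427 | 0.0709 |

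A second simulation gave about 0.065 to 0.075 for the last column, so the overall range is about 6 to 7.5 %. The two-stage rule followed mechanically gives 0.041 to 0.053, against 0.041 to 0.051 for Friedman alone.

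**Step 5: if accrual falls short.** At n = 25, disagreement between Friedman and uncorrected ANOVA under the planned effect is bounded by the two failure rates. In the least favourable scenario (mean 3, rounded, uncorrelated) the bound is (1 − 0.985) + (1 − 0.974) = 0.041. The Trial status section reports eight patients enrolled, and the Discussion says accrual is slower than predicted. With rounded scores and uncorrected ANOVA, the two tests disagree in 7 to 13 % of trials at n = 12 and up to about 16 % at n = 8. Completion by only 8 to 12 patients is an assumption, not a forecast.

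**Step 6: the pairwise choice.** At n = 25 with the mean-7 shape, a 30 % reduction is detected in 100 % of trials by paired t and 99.98 % by Wilcoxon. For a 15 % reduction the figures are 80.1 % and 78.8 %. Power gives little reason to prefer either test, and so little reason to leave the choice open.

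**The case against.** The strongest defence is that the two sections can be read together. The Friedman sentence stands in a list of planning assumptions, while the Data analysis text is generic and has to serve several rating-scale and Likert outcomes. On that reading there is one loosely worded plan. This is possible, but the article does not say which section governs worst pain, and the Sample size wording commits to the test.

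A condensed article may also leave the variable tested for normality and the cut-off to a fuller document. That is accepted: their absence is not part of this point, and the rule in the working is an assumption. A disagreement between two printed statements is not an omission of that kind.

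Three stronger readings are tempting and are not supported:
- **A reader might infer that the 99 % power or N = 25 is unsound.** Steps 1 and 3 show that both stand.
- **A reader might infer that the pre-test itself inflates type I error.** It does not if followed. The 6 to 7.5 % arises only if whichever test is significant is reported, and the protocol does not provide for that, since it ties ANOVA to normality.
- **A reader might argue that Friedman wastes patients,** because its asymptotic efficiency against ANOVA with three conditions is (3/π) × 3/4 = 0.955 × 0.75 = 0.716. That figure assumes normal errors, and the stated power is already Friedman's, so nothing is lost against the plan. In the simulations, Friedman's lowest power (98.5 %) is above ANOVA's lowest (97.4 %).

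Nor does the defect call for a mixed model, which neither section mentions.

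**Conclusion.** The point holds as an inconsistency in the primary analysis. One section fixes Friedman; the other makes the test depend on a normality result and leaves the active-versus-control test open. It is worth correcting before analysis but does not threaten the design.

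With 25 patients, the practical consequence is unpredictability and a possible 1 to 2.5 points of type I error above 5 % if the latitude were used. The choice matters more if few patients complete, when the two tests could lead to different conclusions in about one trial in fourteen (7 %) to one in six (16 %). These sizes rest on assumed control distributions, an assumed normality rule and, for the last range, an assumed number of completers. The inconsistency itself rests on the text alone.

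**What to change.** In the Data analysis section:
- Drop the normality pre-test for worst pain.
- State that the Friedman test at 5 %, as in the Sample size section, is the primary test whatever the distribution, with repeated measures ANOVA as a sensitivity analysis.
- Name one test for active VRET against control, for example the Wilcoxon signed rank test, reported with a median difference and 95 % confidence interval.

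This should be settled before anyone analyses the outcome data. It costs a few sentences. N, the stated power and the conduct of the trial do not change, and the Monte Carlo calculation need not be rerun because it already uses Friedman. The one thing given up is ANOVA as the primary test should the scores look normal; it would still be reported as the sensitivity analysis.

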### Randomisation process

The order of intervention will be randomised using block allocation, as is appropriate for the small sample size [31]. A computer-generated randomisation sequence will use a block size of six, which will be repeated four times.

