A researcher, who has been blinded to the intervention, will return one hour following the dressing change, to collect the questionnaire data from the patient on their experience of pain, anxiety and nausea during their dressing change. Despite the disadvantage of relying on recalled pain by the patient, asking patients questions during the distraction activity could impact the efficacy of the analgesic intervention. Likewise, asking questions during the control condition could be distracting in itself. This methodology will be repeated for the two subsequent dressing changes. At the end of the study period, patients will be offered the use of the VRET system for future dressing changes if they found it beneficial.

The member of the research team present for the dressing change will then undertake a semi-structured interview and questionnaire of the patient and nursing staff to assess their user acceptance of the prototype VRET system.

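### The order of conditions is randomised over three dressing changes, but no named analysis has a period term, so a common trend in pain would inflate the error and cost power, most of all for Friedman

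*Protocol article*

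**What the plan says.** All references are to the protocol article.

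- Randomisation process: "The order of intervention will be randomised using block allocation". Blocks of six are used four times, which gives 24 places. Three conditions have six possible orders.
- Procedure: every patient receives all three conditions, one per dressing change. After the first change, "This methodology will be repeated for the two subsequent dressing changes".
- Data analysis, three conditions: "When comparing the three conditions the repeated measures analysis of variance (ANOVA), assuming normality, or the Friedman test will be used". Each VRET condition is compared with control by a paired t test or, as an alternative, the Wilcoxon signed rank test. Period and sequence are not mentioned.
- Sample size: "a sample size of 25 patients would provide 99 % power to detect a clinically important effect". The test behind that figure is Friedman: "The nonparametric Friedman test (with a significance level of 5 %) will be used to compare the pain scores under the three conditions". The listed assumptions contain no change in pain from one dressing change to the next.
- Outcome measures: time since injury is collected, but only as demographic data.

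**The concern.** The design controls for order and the named analysis then ignores it. The first, second and third dressing changes fall at different stages of healing, and the patient also becomes used to the procedure, so a drift in worst pain is plausible.

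Balanced orders keep such a drift out of the average treatment difference. They do not keep it out of the variability of the within-patient differences, because the gap in time between two given conditions differs from patient to patient. A test without a period term counts that variability as noise. The standard error is then too large for the design, the true type I error falls below 5%, and power falls. The Friedman, Wilcoxon and paired t tests, as named, have no place for a period term.

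The stated 99% power is therefore exposed: it belongs to Friedman and was computed under assumptions with no trend.

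**Working it through.** **Inputs from the protocol (Sample size).** N = 25; Friedman test at 5%; "The mean percentage reduction from the control value is 30 for interactive VRET"; "The mean percentage reduction from the control value is 15 for passive VRET"; "Both percentage reductions are normally distributed with a standard deviation of 25".

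**Assumed, because the protocol does not give them.** The 33 audit scores (0–10 distributions over a range of means); the trend d, in NRS points per dressing change, equal for all patients and centred so that the mean pain level is unchanged; and that each block of six holds each order once.

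**Step 1: the plan's own figure.** With no trend, simulated Friedman power at n = 24 and 25 is 98.1–99.9% over control means from 3.3 to 6.8. The stated 99% is reproduced.

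**Step 2: what a trend adds.** For any two conditions, the six orders put them one change apart in four orders and two changes apart in two. The mean squared gap is (4×1 + 2×4)/6 = 2 and the mean signed gap is 0. The variance of each paired difference therefore rises by 2d², with no shift in its mean.

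Take n = 24, an assumed within-patient SD of 1.5, and d = 1:

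- SE used by the unadjusted test: √[(2×1.5² + 2×1²)/24] = √(6.5/24) = 0.52.
- True SE of the balanced estimate: √(2×1.5²/24) = √(4.5/24) = 0.43.
- Simulated type I error without period: about 1.5–2% against a nominal 5%. With period in the model it stays at about 5%.

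**Step 3: power under the plan's effect model.** Four blocks of six; each range runs over assumed control means of 5 and 7.

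| d per change | Friedman | ANOVA, no period | ANOVA with period |
|---|---|---|---|
| 0.5 | 96–99.5% | – | – |
| 1 | 67–94% | 93–99.6% | 99.6–99.9% |
| 1.5 | 21–64% | 66–95% | about 99–99.7% |

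The planned active-versus-control paired t test keeps 98.7–99.9% at d = 1. At d = 1.5 it loses up to about 11 percentage points.

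**Step 4: a second simulation with other assumed scores.** N = 25, control mean 5, SD about 2.5. The last column is the ANOVA residual SD without period divided by that with period, which is also the ratio of interval widths.

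| d | Friedman | ANOVA, no period | ANOVA with period | Ratio |
|---|---|---|---|---|
| 0 | 99.5% | 99.5% | 99.4% | 1.00 |
| 0.5 | 97.7% | 99.1% | 99.6% | 1.07 |
| 1 | 84.5% | 96.0% | 99.5% | 1.24 |
| 1.5 | 51.7% | 83.1% | 99.5% | 1.46 |

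The two sets differ in sample size and in the simulated scores, so single figures should not be leaned on. The pattern is the same: Friedman suffers most, ANOVA less, and the model with period hardly at all. With no trend, the period term costs next to nothing.

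**Step 5: incomplete patients.** If m of the 24 remain at random, the SD of the active-minus-control difference in mean period is √[(2/m)×(24−m)/23]. For m = 15 this is √(0.1333×0.3913) = 0.23; for m = 8 it is √(0.25×0.6957) = 0.42. Multiplied by d, that is the typical shift in an unadjusted contrast. A period term removes it where the trend is common to patients.

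**The case against.** The case for leaving the plan alone has real strength.

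- **The trend has no source.** The protocol gives none. At 0.5 points per change little is lost. A trend of 1.5 means a fall of 2×1.5 = 3 points from first to third change, which on a mean of 5 is twice the 30% treatment effect (1.5 points), although the Background says wound care is often daily. This stands, and is why the result is given as a range.
- **Much of the loss is specific to Friedman.** Setting unadjusted Friedman against a period-adjusted active-versus-control contrast changes rank to parametric, three-way to pairwise, and unadjusted to adjusted all at once. This stands; the like-for-like ANOVA and paired t figures are the fair ones.
- **A period term removes only the common trend.** With patient-specific slopes (mean 0.5, SD 1, control mean 5), simulated ANOVA power was 84% without period and 87% with it. This stands.
- **Not all lost power comes from omitting period.** If pain falls from its starting level, a floor effect lowers adjusted power too: 92–99.9% at 1 point per change.
- **The ANOVA may be fuller than it looks.** The protocol does not call it one-way. A repeated measures ANOVA with sequence as a between-patient factor would remove a common period effect (99.4% against 99.4% for the period model at d = 1, mean 5), and such detail may sit in a fuller document. This stands for the ANOVA branch only.

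A reader might also infer that the treatment comparison is biased or that false positives become likelier. Neither follows: with balanced orders the estimate is unbiased, and the error is in the conservative direction. Nor does the protocol support saying that the 99% is miscalculated; it reproduces under its own assumptions. And the protocol does not mention confidence intervals, so the widening applies only to those that would accompany the ANOVA or paired t test.

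**Conclusion.** The point holds as a loss of efficiency and should be fixed, but it is not critical. The named analyses do not carry period through from a design that randomises order over three successive changes. At an assumed common trend of 1 NRS point per change, actual type I error is about 1.5–2% (within-patient SD 1.5), and the power of Friedman, the test behind the stated 99%, falls to 67–94%. For the same trend the three-condition ANOVA loses between a fraction of a point and about seven points, and the active-versus-control paired t test about one point or less. Losses are small at 0.5 points and large only for steep trends.

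These sizes rest on an assumed trend, assumed audit scores and a trend shared by all patients. Incomplete data add a reason to act. The Discussion says that the most suitable patients are often discharged before all three stages, and Trial status reports eight enrolled. If started patients fail to complete, balance of orders can no longer be relied on.

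**What to change.** In Data analysis, make the primary analysis of worst pain a linear mixed model with condition and period (dressing change 1, 2 or 3) as fixed effects and patient as a random effect. Report the active-minus-control difference with its 95% CI from that model. Keep Friedman and Wilcoxon as sensitivity analyses. In Sample size, state that the 99% assumes no trend across dressing changes.

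The change is one of wording. Session order is already recorded by the randomisation, and the model can be fitted in the same software. It costs two degrees of freedom and makes the primary result rely on a linear model for a bounded 11-point score, which is why the rank tests are worth keeping alongside. The term will not remove patient-specific trends.

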## Discussion

The study accrual rate is currently slower than predicted by previous audits of admission data. A review of the screening log has found that recruitment has been limited by the nature of burn care, the ability of burn inpatients to provide informed consent and the ability of patients to use the VR equipment.

The within-subject design with graded exposure to the VR intervention was chosen to reduce bias within the study, as it reduces the effect of patient-related confounding factors, such as biopsychosocial influences. Unfortunately this design may have consequently reduced the feasibility of accruing participants.

Each patient has to receive at least three inpatient dressing changes not requiring a general anaesthetic or ketamine. Those patients who are otherwise well enough to be discharged home return to outpatient clinic for dressing changes, so many only undergo a one or two study-appropriate dressing change following skin grafting and prior to discharge. For logistical reasons, the study is not currently being run in the outpatient clinic. A relatively high proportion of burn patients with longer lengths of stay have self-harmed (mean 22 days). As many as 82 % suffer from mental illness [33], with many excluded from the study due to the inability to provide informed consent or an unwillingness to take part. In summary, those most suitable for enrolment in the trial are usually those who are discharged the earliest so are unable to complete all three stages of data collection. In order to improve the recruitment rate, future trial designers could reduce the number of required dressing changes to two. This would allow a within-subject comparison of control conditions and either passive or active VR for each patient, albeit with a larger sample size. The research team should be aware that prison inmates can be enrolled, as the study does not continue when the patient is returned to prison.

The majority of surviving patients with a longer length of stay are the older patients (mean 23 days), those with medical comorbidities and those with large burns [33–35]. Whilst increasing age is associated with higher mortality for a given percentage of burn, this rate is improving and there are increasing numbers of older survivors of burns [34]. Over half of the over 65s admitted to the burn unit are treated conservatively [35]. All these patients are screened, and many undergo the prerequisite number of appropriate dressing changes; however, many have been found to be too frail to attempt to use the VR system. This finding needs to be explored further. Future studies should include a thorough patient capabilities and ergonomics assessment, as part of the human-centred design process [22], prior to undertaking clinical trials.

